# Transitional Care Support for Medicaid-Insured Patients With Serious Mental Illness: Protocol for a Type I Hybrid Effectiveness-Implementation Stepped-Wedge Cluster Randomized Controlled Trial

**DOI:** 10.2196/64575

**Published:** 2024-11-12

**Keywords:** serious mental illness, health care disparities, Medicaid, evidence-based practice, implementation science, socioeconomic disparities in health

## Abstract

**Background:**

People diagnosed with a co-occurring serious mental illness (SMI; ie, major depressive disorder, bipolar disorder, or schizophrenia) but hospitalized for a nonpsychiatric condition experience higher rates of readmissions and other adverse outcomes, in part due to poorly coordinated care transitions. Current hospital-to-home transitional care programs lack a focus on the integrated social, medical, and mental health needs of these patients. The Thrive clinical pathway provides transitional care support for patients insured by Medicaid with multiple chronic conditions by focusing on posthospitalization medical concerns and the social determinants of health. This study seeks to evaluate an adapted version of Thrive that also meets the needs of patients with co-occurring SMI discharged from a nonpsychiatric hospitalization.

**Objective:**

This study aimed to (1) engage staff and community advisors in participatory implementation processes to adapt the Thrive clinical pathway for all Medicaid-insured patients, including those with SMI; (2) examine utilization outcomes (ie, Thrive referral, readmission, emergency department [ED], primary, and specialty care visits) for Medicaid-insured individuals with and without SMI who receive Thrive compared with usual care; and (3) evaluate the acceptability, appropriateness, feasibility, and cost-benefit of an adapted Thrive clinical pathway that is tailored for Medicaid-insured patients with co-occurring SMI.

**Methods:**

This study will use a prospective, type I hybrid effectiveness-implementation, stepped-wedge, cluster randomized controlled trial design. We will randomize the initiation of Thrive referrals at the unit level. Data collection will occur over 24 months. Inclusion criteria for Thrive referral include individuals who (1) are Medicaid insured, dually enrolled in Medicaid and Medicare, or Medicaid eligible; (2) reside in Philadelphia; (3) are admitted for a medical diagnosis for over 24 hours at the study hospital; (4) are planned for discharge to home; (5) agree to receive home care services; and (6) are aged ≥18 years. Primary analyses will use a mixed-effects negative binomial regression model to evaluate readmission and ED utilization, comparing those with and without SMI who receive Thrive to those with and without SMI who receive usual care. Using a convergent parallel mixed methods design, analyses will be conducted simultaneously for the survey and interview data of patients, clinicians, and health care system leaders. The cost of Thrive will be calculated from budget monitoring data for the research budget, the cost of staff time, and average Medicaid facility fee payments.

**Results:**

This research project was funded in October 2023. Data collection will occur from April 2024 through December 2025. Results are anticipated to be published in 2025-2027.

**Conclusions:**

We anticipate that patients with and without co-occurring SMI will benefit from the adapted Thrive clinical pathway. We also anticipate the adapted version of Thrive to be deemed feasible, acceptable, and appropriate by patients, clinicians, and health system leaders.

**Trial Registration:**

ClinicalTrials.gov NCT06203509; https://clinicaltrials.gov/ct2/show/NCT06203509

**International Registered Report Identifier (IRRID):**

DERR1-10.2196/64575

## Introduction

### Background

Approximately 10 million adults in the United States have a serious mental illness (SMI; ie, major depressive disorder, schizophrenia, and bipolar disorder) [1]. Medicaid, as the largest payer of mental health services, covers 26% of nonelderly adults with SMI [2]. However, up to half of Medicaid-insured individuals with comorbid SMI experience unmet treatment needs [3]. Our population of interest is Medicaid-insured individuals who are hospitalized for a medical condition but live with comorbid SMI. They experience worse health outcomes, particularly following hospitalization due in part to care fragmentation and a lack of connection to community-based services [4,5]. Such disparities are rooted not only in the complexities of their psychiatric conditions but also in a health care system that often fails to provide comprehensive and integrated care. Hospital-to-home transitional care programs can improve postdischarge outcomes through a focus on continuity of care; however, most of these programs often focus on specific medical conditions and lack comprehensive plans to address co-occurring mental health diagnoses [6-8]. Similarly, SMI-focused transitional care programs often exhibit a critical gap; they do not also have a comprehensive plan to address co-occurring chronic medical conditions [9-11]. This oversight is significant given the complex needs of individuals with SMI, who frequently face concurrent medical conditions that require integrated care approaches. In addition, existing transitional care models for patients with SMI who are admitted for psychiatric or nonpsychiatric reasons do not adequately address the social determinants of health (SDOH), a critical driver of optimal health and well-being [12,13]. The SDOH, including factors such as housing stability, employment, social support, and access to nutritious food, significantly influences health outcomes yet remains peripheral in many transitional care strategies. The absence of a holistic approach in these transitional care models underscores the necessity for integrating SMI care with physical health management and addressing the SDOH.

The Thrive clinical pathway addresses the SDOH for Medicaid-insured individuals with multiple chronic conditions transitioning from hospital to home through intensive virtual case coordination, home care services, connections to community-based services, and supervision provided by the discharging clinician for up to 30 days (Figure 1).

Through this process, Thrive increases connections to community-based services and providers (ie, primary and specialty care) and decreases unfavorable posthospital use (ie, readmissions and emergency department [ED] visits). In a pilot study comparing 42 Thrive participants to 437 patients receiving usual care, we found a 50% reduction in 30-day hospital readmissions and a 50% increase in access to postdischarge primary care and specialty care [14].

**Figure 1 figure1:**
[figure not shown]
Components of the Thrive clinical pathway. APP: advanced practice provider; EHR: electronic health record; MD: medical doctor; OT: occupational therapy; PRN: pro re nata (as needed); PT: physical therapy; RN: registered nurse; SW: social worker.

### Enhancing Thrive: Integrating Serious Mental Illness

During the successful launch of Thrive at a single site, we also noted a sizable co-occurrence of SMI among our Thrive participants. This raised concerns over additional barriers they might face following hospitalization [15] and whether they experienced similar benefits from the Thrive intervention compared with participants without an SMI diagnosis. In an observational pilot study comparing utilization outcomes of Thrive participants with and without SMI, there were no statistically significant differences between the groups for 30-day readmissions and ED use. However, in qualitative interviews, Thrive participants revealed that while they were happy with the care provided for their medical conditions and with connections to social services, their behavioral health needs were not fully assessed or addressed ([name], 2024, unpublished data).

Building on these pilot findings, we now seek to adapt Thrive to ensure suitability for all patients insured by Medicaid including those with co-occurring SMI. Therefore, we are conducting a type I hybrid effectiveness-implementation, stepped-wedge, cluster randomized controlled trial at a new clinical site [16]. Our study is informed by Woodward’s Health Equity Implementation Framework (HEIF), which centers equity within the implementation process and focuses on the culturally relevant factors of recipients, the patient-provider interaction, and the societal and organizational context [17].

### Aims and Hypotheses

The specific aims of this research are to engage staff and community advisors in participatory processes to (1) prioritize additional components to the current Thrive care model suitable for participants with co-occurring SMI and evaluate the context required for adaptation of the intervention; (2) examine utilization outcomes (ie, Thrive referral; readmission; and ED, primary, and specialty care visits) for Medicaid-insured individuals with and without SMI who receive Thrive compared with usual care—we hypothesize that individuals with SMI who receive usual care will have worse utilization outcomes compared with those without SMI and that all individuals receiving Thrive with and without SMI will have better outcomes compared with those with usual care; and (3) evaluate the acceptability, appropriateness, feasibility, and cost-benefit of an adapted Thrive clinical pathway that is tailored for Medicaid-insured patients with co-occurring SMI.

## Methods

### Overview

This study will use a prospective, type I hybrid effectiveness-implementation, stepped-wedge, cluster randomized controlled trial design. The advantage of this trial design is that it offers an efficient and practical way to introduce Thrive at a new clinical site while reducing the ethical concerns of withholding an intervention that has shown benefit for economically disadvantaged populations [14]. We will conduct our study in accordance with the Standard Protocol Items: Recommendations for Interventional Trials (SPIRIT) statement and the Consolidated Standards of Reporting Trials (CONSORT) extension for stepped-wedge cluster randomized trials [18,19]. These guidelines ensure rigorous and transparent reporting of our trial design and outcomes and the checklists are included as Multimedia Appendices 1 and 2. Our use of a mixed methods (quantitative + qualitative) study design prioritizes quantitative data to evaluate program referrals, outcomes, and fidelity. Qualitative data will enrich our understanding of barriers and facilitators faced by health care providers in implementing the expanded Thrive intervention, particularly with the addition of mental health services [20]. Taken together, the findings from both the quantitative and qualitative approaches will allow for future intervention refinement if needed and determining the implementation strategies associated with adoption and sustainability. Multimedia Appendix 3 provides a study overview, and the methodology of each aim will be described.

### Study Setting

This study is set at the Cedar location of the Hospital of the University of Pennsylvania (HUP), part of the University of Pennsylvania Health System and a new site to implement Thrive. HUP-Cedar is located in West Philadelphia and serves as a safety net primarily treating the most socially at-risk residents of Philadelphia. Over half the patients at this 45-bed hospital are Medicaid or dually Medicare and Medicaid insured, and the majority are from diverse racial and ethnic minority backgrounds.

### Aim-1 Methods

Aim 1 is to engage staff and community advisors in participatory processes to (1) prioritize additional components to the current Thrive care model suitable for participants with co-occurring SMI and (2) evaluate the context required for adaptation of the intervention. The preimplementation process used to meet aim 1 is described extensively elsewhere ([name], 2024, unpublished data).

### Aim-2 Methods

Aim 2 is to examine utilization outcomes for Medicaid-insured individuals diagnosed with and without SMI who receive Thrive services compared with usual care.

### Design and Randomization

The stepped-wedge cluster design accounts for the proportion of the study period that each group spends in the control and intervention periods (Table 1).

Randomization will occur at the unit level. There are 2 units at HUP-Cedar; using a random number generator, the first unit will be chosen. Eight weeks later, the second unit will begin Thrive referrals. Each unit has 1 case manager and 1 social worker responsible for discharge planning and initiating Thrive referrals. Due to the small number of clinicians and their shared workspace, all 4 will be trained simultaneously, and concealing allocation will not be feasible.

**Table 1 table1:** Study diagram for the type I hybrid effectiveness-implementation, stepped-wedge, cluster randomized controlled trial of the adapted Thrive clinical pathway for serious mental illness.

Cluster	Baseline (3 months)	Enrollment period 1 (two months)	Enrollment period 2 (two months)	Follow-up (17 months)
Sequence 1 (first unit)		✓	✓	✓
Sequence 2 (second unit)			✓	✓

### Study Population

Eligibility criteria for Thrive referral include individuals who (1) are Medicaid insured, dually enrolled in Medicaid and Medicare, or Medicaid eligible; (2) reside in Philadelphia; (3) are admitted for a medical diagnosis for over 24 hours at the study hospital; (4) are planned for discharge to home; (5) agree to receive home care services; and (6) are aged 18 years or older. Patients with SMI will be identified using the *International Classification of Diseases, Tenth Revision* (*ICD-10*) codes for major depressive disorder, bipolar disorder, or schizophrenia in secondary diagnoses [21]. Exclusion criteria include referral to palliative or hospice home care services at discharge.

### Current Usual Care

Usual care includes a discharge to the patient’s home with standard discharge care planning that addresses the patient’s medical needs. This may or may not encompass referrals to home care and other outpatient services as appropriate.

### Thrive Intervention Group

Patients are referred to Thrive by nurse case managers or social workers during the hospital discharge planning process. They are alerted to a potential Thrive referral by an electronic health record (EHR) flag developed by our team [22]. Thrive participants agree to home care services through Penn Medicine at Home. A home care nurse visits the patient within 72 hours of discharge. This visit includes medication reconciliation, review of discharge orders, setting person-centered goals, and referral to other home care services (eg, physical therapy) as deemed necessary. The nurse also determines the visit frequency based on the patient’s needs, ranging from 1-3 visits per week. All Thrive participants receive a social work referral, and their psychosocial and mental health needs are further assessed and connections to community resources are provided. Home care nurses provide patient updates to the discharging provider (eg, a medical doctor or advanced practice provider) following the first home visit. Extended supervision by the discharging provider is provided for up to 30 days or until Thrive participants have been seen by their primary care provider. A key feature of Thrive is the intensive, equity-focused, 30-day case management provided during weekly virtual interdisciplinary case conferences. These meetings focus on assessing and addressing the SDOH such as housing, food insecurity, and substance use services as needed. If a source of primary care is absent, we work to link Thrive participants to community providers. Additional Thrive services will be provided as determined by the work group (Aim 1).

### Data Collection and Sources

Clinical data, outcome metrics, and postacute care service use will be derived from the EHR at baseline and throughout the Thrive referral period. The characteristics of Thrive participants will be captured in weekly case conferences and stored in a University of Pennsylvania REDCap (Research Electronic Data Capture; Vanderbilt University) system database. Data for the usual care group will be derived from the EHR. The study timeline is outlined in the SPIRIT diagram (Figure 2).

**Figure 2 figure2:**
[figure not shown]
SPIRIT (Standard Protocol Items: Recommendations for Interventional Trials) diagram—Thrive schedule of evaluations. ED: emergency department; PCP: primary care provider.

### Variables and Measures

The primary independent variable is participation in Thrive. The outcome variables include Thrive referral rates; 30-, 60-, and 90-day readmissions and ED visits; and receipt of primary and specialty care within 30 days of index hospitalization [23-25]. For Thrive participants, these outcomes will be assessed from the date of hospitalization that resulted in a referral to Thrive. For the usual care group, we will identify all readmission and ED visits occurring after the first index hospitalization identified in the EHR from the calendar year of the study. Additional covariate data at both the patient (eg, demographics, comorbidities, or mental health diagnoses) and unit levels (eg, type of unit, discharging team, or provider) will be collected.

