### Analysis

Monthly reports will be generated to monitor referral patterns to the Thrive clinical pathway. The primary analysis will use a mixed-effects negative binomial regression model, accounting for both medical team and time effects, to evaluate readmission and ED utilization patterns comparing those with and without SMI who receive Thrive to those with and without SMI who receive usual care [26,27]. Sensitivity analyses may include logistic regression, depending on data distribution.

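### The primary analysis compares Thrive participants with usual-care patients, not the randomised unit conditions, and only participants must have agreed to home care

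*Protocol article*

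**What the plan says.** Design and Randomization: "Randomization will occur at the unit level". There are two units, and the second starts referrals eight weeks after the first. What is randomised is the order in which units start.

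Variables and Measures: "The primary independent variable is participation in Thrive". The Analysis section under Aim 2 gives the primary contrast as "comparing those with and without SMI who receive Thrive to those with and without SMI who receive usual care", in a mixed negative binomial model "accounting for both medical team and time effects". The Power Analysis also splits its totals into Thrive participants and usual care: 236 and 236 for readmissions, 267 and 267 for ED visits.

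Study Population words its list as "Eligibility criteria for Thrive referral include individuals who" meet six conditions. The fifth is that they "agree to receive home care services". Thrive Intervention Group adds that case managers or social workers make the referral and that "Thrive participants agree to home care services through Penn Medicine at Home".

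Current Usual Care is discharge home with standard planning, of which it says "This may or may not encompass referrals to home care and other outpatient services as appropriate". Variables and Measures identifies this group by the first index hospitalisation in the record during the study's calendar year. Thrive participants are instead indexed at the hospitalisation that led to referral.

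**The concern.** A cluster randomised trial supports a causal claim because allocation, not the patient or the discharge planner, decides who belongs to which group. Here a patient enters the Thrive group only after being referred by staff and agreeing to home care. Neither step is stated for the comparator. If patients who agree, or whom staff choose to refer, differ in their underlying risk of readmission or ED use, the primary estimate mixes that difference with the effect of Thrive.

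The usual-care rule adds a second difficulty. It is not limited to control unit-periods, and the article does not say where eligible patients on an active unit are counted if they decline or are not referred.

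At stake is whether the main result can be reported as randomised evidence. Strengths and Limitations names the stepped-wedge cluster randomised design as the study's chief strength.

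**Working it through.** **1. Allocation and analysis side by side**

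| Feature | Randomised comparison | Primary analysis |
|---|---|---|
| Exposure | Unit's condition at a given time | Patient's participation or receipt |
| Who decides it | Random number generator | Staff referral and patient agreement |
| Agreement to home care | Plays no part in allocation | Required for Thrive, not stated for usual care |
| Index stay | Not specified separately | Referral stay (Thrive); first stay in calendar year (usual care) |
| Source of controls | Control unit-periods in Table 1 | Calendar-year record rule |

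The exposure, the contrast and the sample-size split all use participation or receipt. No analysis by assigned unit-period is described, and the only sensitivity analysis named is logistic regression. The model names team and time effects, not the assigned condition.

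**2. The plan's own sample size**

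The totals of 472 and 534 can be neither confirmed nor refuted, because the Power Analysis states no Thrive effect size. Taking its 28% overall readmission rate as the usual-care risk (an assumption), 236 per group at 80% power and two-sided 0.05 corresponds to 28% versus 17.2%, a risk ratio of 0.62. The point about exposure does not depend on this.

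**3. Can selection alone move the estimate? (assumed inputs)**

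Suppose Thrive has no effect, usual care is a mix with 28% risk, a share a of patients would accept home care, and acceptors have r times the risk of decliners. Decliner risk is 0.28/(a·r + 1 − a), so the apparent risk ratio is r/(a·r + 1 − a). For a = 0.5 and r = 0.6 this is 0.6/0.8 = 0.75.

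| Acceptance a | r = 0.6 | r = 0.8 | r = 1.25 |
|---|---|---|---|
| 30% | 0.68 | 0.85 | 1.16 |
| 50% | 0.75 | 0.89 | 1.11 |
| 70% | 0.83 | 0.93 | 1.06 |

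The documents give neither a nor r. The table shows only that the bias can run either way and, under some inputs, comes near the back-solved 0.62.

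**4. Power cost of analysing by assigned condition**

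Assume 28% under usual care and 14% among participants (the pilot's 50% reduction), with non-participants staying at 28%. At uptake u, the Thrive-period risk is p2 = 0.28 × (1 − 0.5u). With p1 = 0.28 and p̄ the mean of p1 and p2,

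n per group = [1.96·√(2p̄(1 − p̄)) + 0.8416·√(p1(1 − p1) + p2(1 − p2))]² / (p1 − p2)².

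| Uptake | p2 | n per group | Total |
|---|---|---|---|
| 100% | 14.0% | 132 | 264 |
| 70% | 18.2% | 290 | 580 |
| 50% | 21.0% | 592 | 1,184 |
| 30% | 23.8% | 1,707 | 3,414 |

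At 50%: p̄ = 0.245; (1.192 + 0.510)² = 2.898; 2.898/0.0049 = 591.4, rounded up to 592. These totals come before clustering and loss to follow-up. The article gives no uptake figure.

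**The case against.** The strongest defence has three parts. First, the model includes team and time effects, patient and unit covariates are collected, and referral rates are an outcome with monthly monitoring. These may reduce confounding. But adjustment does not recreate the allocated comparison, and neither willingness to accept home care nor staff choice is among the covariates given as examples.

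Second, with two units and one eight-week step, randomisation protects little even if used. This stands. In Table 1 the units differ in condition only during the first two-month enrolment period; the rest of the contrast depends on adjustment for time. Analysis by assigned condition still takes patient agreement and staff referral out of the definition of exposure.

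Third, that analysis is diluted by non-uptake and may have little power. This also stands and must be stated as a cost.

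Four stronger readings are tempting but unsupported:

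- A reader might divide 267 by 8 control unit-months (33.4) and 267 by 40 Thrive unit-months (6.7) and infer that about 20% of eligible patients take part. Two equal power targets give 8/40 = 20% whatever the uptake. The sum also assumes that controls come only from control periods and that the 17-month follow-up column enrols patients.
- A reader might infer that the bias favours Thrive. No figure in the article supports a direction; if acceptors are sicker, it runs against Thrive.
- A reader might infer that patients readmitted before the first home visit drop out of the Thrive group. Nothing makes that visit a condition of being counted, and outcomes run from the hospitalisation that led to referral.
- A reader might call the usual-care group wholly unselected, or say that decliners certainly enter it. The group is Medicaid-insured and discharged home; which other criteria apply, and where decliners go, is not stated.

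**Conclusion.** The point holds for the definition of the exposure and for the unequal home-care condition. The article itself fixes participation as the primary exposure, so this is not a detail left to an analysis plan. The primary contrast is as-treated and is not the comparison that was randomised.

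The size and direction of any bias are unknown. The risk ratios of 0.68 to 1.16 under no effect rest wholly on assumed acceptance shares and risk ratios, and show possibility, not expectation. The conclusion needs none of them: it follows from what is randomised, what is analysed and who can enter each group. It should be settled before outcomes are compared.

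**What to change.** 1. **Primary exposure.** Define it as the unit's assigned condition (usual-care or Thrive period) on the index discharge date. Include every discharge that meets criteria 1 to 4 and 6 and is not excluded, whether or not the patient was referred or agreed to home care. Apply one index-hospitalisation rule in both conditions.
2. **Participation.** Keep it as a secondary analysis labelled observational. Draw controls only from control unit-periods, restrict them to patients discharged home with home care accepted, and adjust for the collected baseline covariates. Never count non-participants from a Thrive period as usual care.
3. **Power.** Restate the Power Analysis for the assigned-condition contrast, with an explicit usual-care risk, Thrive effect and range of uptake.
4. **Claims.** State in Strengths and Limitations that two units and one step give limited randomised protection.

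The data cost is small: a wider extract from the health record, for whose clinical data the article reports a waiver of consent. The statistical cost is not small. The diluted estimate may need far more than the planned 534 patients: about 580 at 70% uptake or 1,184 at 50% under the assumptions above, before clustering and loss. If that is out of reach, the article should say that the assigned-condition estimate will be imprecise, and should not present the participation contrast as the randomised result.

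### A usual-care patient referred to Thrive at a later readmission keeps accruing usual-care events and can also enter the Thrive group; the dilution is probably modest, but each patient should enter once

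*Protocol article*

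**What the plan says.** All references are to the protocol article.

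- **Crossover (Design and Randomization, Table 1).** "There are 2 units at HUP-Cedar; using a random number generator, the first unit will be chosen". After a three-month baseline that unit goes live. "Eight weeks later, the second unit will begin Thrive referrals".
- **Outcomes (Variables and Measures).** These include "30-, 60-, and 90-day readmissions and ED visits".
- **Exposure (same section).** "The primary independent variable is participation in Thrive".
- **Where counting starts (same section).** For Thrive patients it starts at the hospitalisation that produced the referral. For the comparator: "For the usual care group, we will identify all readmission and ED visits occurring after the first index hospitalization identified in the EHR". The usual-care index stay is taken from the study's calendar year and is not limited to the unit's control phase.
- **Who can get Thrive (Study Population; Thrive Intervention Group).** A patient needs a qualifying medical stay of more than 24 hours, a planned discharge home, agreement to home care, and a referral by a case manager or social worker.

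**The concern.** The two counting rules do not fit the crossover timetable. A patient discharged under usual care shortly before the switch can be readmitted after it and referred to Thrive at that second stay. Two things follow from the rules as written.

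1. Events after the second stay, but inside the first stay's window, remain usual-care events although the patient is now on Thrive. If Thrive works, this pulls the contrast towards no difference. It does so among repeat users, who contribute most to a count model.
2. The second stay is also one that led to a referral, so the patient meets the Thrive definition too. One person can then sit in both groups, with the same events counted in each. The groups are no longer independent. The model described under Analysis names medical team and time effects and no patient-level term.

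**Working it through.** **Timetable.** The Table 1 periods sum to 3 + 2 + 2 + 17 = 24 months, which matches the 24 months of data collection in the Abstract. The step is 8 × 7 = 56 days in the text and two months (about 61 days) in the table, which agree to rounding.

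**One patient under the stated rules (constructed example).** Unit 1 switches at day 91.
- Day 60: discharged under usual care.
- Day 100: readmitted and referred to Thrive. This is day 40 of the first window and a valid usual-care event.
- Day 105: discharged on Thrive.
- Day 125: readmitted again. This is day 65 after the first discharge, so it is a 90-day usual-care event. It is also day 25 from the referral admission (day 20 from that discharge), so it is a 30-day Thrive event.

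The day-125 event is counted in both groups.

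**How often a window passes the switch.** Control time L is 91 days on unit 1 and 91 + 56 = 147 days on unit 2. Assume uniform discharges and equal daily volume. The share of patients whose window w passes their own unit's switch is w/L, pooled as 2w/(91 + 147) = 2w/238. The mean share of window time after the switch is w/(2L), pooled as w/238.

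| Window | Unit 1 | Unit 2 | Pooled patients | Pooled window time |
|---|---|---|---|---|
| 30 days | 30/91 = 33% | 30/147 = 20% | 60/238 = 25% | 30/238 = 13% |
| 60 days | 60/91 = 66% | 60/147 = 41% | 120/238 = 50% | 60/238 = 25% |
| 90 days | 90/91 = 99% | 90/147 = 61% | 180/238 = 76% | 90/238 = 38% |

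With a 61-day step the denominator becomes 91 + 152 = 243, and the pooled patient shares are 25%, 49% and 74%, so the choice hardly matters.

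**From overlap to affected events.** An open window is not exposure. Exposure needs a new stay after the switch, then referral and agreement. A simulation illustrates the size under these assumptions:
- daily readmission hazard for the first 30 days after a discharge of −ln(1 − 0.28)/30 = 0.011, from the 28% 30-day rate under Power Analysis;
- hazard after day 30 at 100%, 50% or 25% of that;
- up to three readmissions, with 5 days added before each repeat;
- uptake of Thrive at a post-switch readmission of 100%, 50% or 20%;
- the patient's own unit's switch only.

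Uptake, the later hazard and the 5 days are assumptions; the article gives none of them.

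| Window | Patients with a readmission after the switch | Readmissions following a Thrive start, as share of all usual-care readmissions |
|---|---|---|
| 30 days | about 4% | 0.2-0.8% |
| 60 days | 7-13% | 0.7-3.6% |
| 90 days | 12-27% | 1.1-8.0% |

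The simulation leaves out ED visits, unit 2 patients readmitted to unit 1 while only unit 1 is live, and the effect of counting a patient in both groups. It covers control-phase patients only.

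**The case against.** **Overlap is not contamination.** A patient at home is not treated because the ward has begun referrals. This stands. A reader might infer from the 76% that most usual-care follow-up is contaminated, or that readmitted usual-care patients simply receive Thrive. The documents support neither: receipt needs an eligible stay, referral and agreement to home care. Only 46 patients had been referred by October 17, 2024 (Results), and the article gives no denominator from which to derive uptake.

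**The 28% rate.** A reader might also infer that more than a quarter of usual-care patients have a second stay at which referral can happen. That ignores that the stay must fall after the switch. Within 30 days the illustrative figure is about 4%, and at 90 days a quarter is reached only if the hazard does not decline. The 28% is also an overall rate, not a usual-care rate.

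**The step length.** That 60 and 90 days exceed 56 days is true but does not decide the matter. What counts is the time from discharge to the unit's switch, which is why early baseline discharges are mostly unaffected at 60 days and some 30-day windows are affected.

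**Left to the analysis plan.** Rules for patients who qualify twice are often set in an analysis plan, which is not at hand, and the article does not say that anyone is to be kept in both groups. So planned double counting cannot be asserted, only that the wording permits it. The objection does not dispose of the point, because the article does state a rule: all later events count, from a different origin in each group. That rule conflicts with its own crossover.

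**A policy comparison.** Keeping patients in their original condition is defensible, with some dilution accepted. This stands and shapes the fix. It does not justify entering the same patient again as a Thrive case.

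**Conclusion.** The point holds in a limited form. The counting rules let events after a later Thrive referral stay in usual care, and let the same patient and events enter the Thrive group. The triggering readmission is properly a usual-care event; only what follows it within the window is affected. Dilution is probably modest: about 1-8% of usual-care readmissions at 90 days, 0.7-3.6% at 60 days and under 1% at 30 days. The upper end at 90 days needs full uptake and an undiminished readmission hazard.

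These figures rest on uniform discharges, equal unit volumes and assumed uptake. They describe control-phase patients, whereas the article draws usual care from the calendar year. An eligible patient not referred on a live unit and referred at a later stay raises the same problem, so it is not confined to the weeks around the switch. Dual membership needs only one such patient, whatever the amount of dilution. The point is worth correcting before the analysis planned for early 2026, but it does not by itself undermine the trial.

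**What to change.** State in the protocol and apply in the analysis dataset:

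1. Each patient enters once, indexed at the first eligible stay, by the same rule in both groups.
2. The patient is classified by the unit's randomised condition at that discharge and stays in that group for the full 30-, 60- or 90-day window, with the all-events count as the main outcome.
3. A usual-care patient referred later is not re-entered as a Thrive case.
4. Report how many usual-care patients were later referred to Thrive within each window.
5. Add a sensitivity analysis that stops counting at the start of Thrive, or at the first readmission in both groups, with person-time as offset. Stopping at first readmission should not be the main analysis: it discards valid repeat events and ends ED counts at an outcome that treatment may affect.

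**Cost.** Only wording and data derivation change, since encounters come from the EHR and referrals are already monitored. Some dilution remains in the main analysis. Patients whose first eligible stay was under usual care no longer count as Thrive participants, so fewer count towards the target of 267. Classifying by unit condition also replaces participation as the main exposure, so eligible patients not referred on a live unit fall in the Thrive condition.
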